**RESEARCH PLAN**

We will perform the clinical studies at i) Alexishafen and Mugil Clinics, Madang Province, sites we have used for various studies since 2001 and which have proven recruitment potential and excellent facilities,CIA#31 and ii) Vunapope Hospital, East New Britain Province which also has a busy clinical load and laboratories which have been used by the PNG Institute of Medical Research (IMR) for malaria studies. Maprik in the East Sepik may be brought in as an additional site depending on recruitment. Laboratory studies (host/parasite genotyping, drug assays and/or biochemical testing) will be conducted at Vunapope; the IMR laboratories at Yagaum Hospital, Madang Province; the University of Western Australia (UWA) School of Medicine and Pharmacology and the Biochemistry Department at Fremantle Hospital; the Pharmacy School, Curtin University. Relevant techniques are well established in these institutions.

**Main Study: A trial of the tolerability, safety, efficacy and cost-effectiveness of AL, AP and AN in PNG children with uncomplicated falciparum or vivax malaria** *(Primary aim)*

*Background:* Since pyronaridine11-14 and naphthoquine16 are active against CQ-resistant falciparum malaria and have a t½*e* that is at least that of lumefantrine (4-6 days), AP and AN should have similar efficacy over 42 days of follow-up to AL in this situation. We postulated that the greater efficacy of DP vs AL against *P. vivax* reflects, in part, the longer piperaquine t½*e* (3-4 weeks), in which case the efficacy of AP and perhaps AN should equate with that of DP. However, the similar low efficacy of AL and CQ-SP in areas with known CQ-resistant *P. vivax* means that other factors may underlie the poor response to AL in our recent trial.8

*Operational principles:* We will conduct the study using standard operating procedures, under Good Clinical Practice guidelines, in accordance with the Helsinki Declaration, and with ethical approval from the PNG Ministry of Health Medical Research Advisory Committee and the UWA Human Research Ethics Committee. Although the trial is open-label, there will be an independent Data and Safety Monitoring Committee (DSMC) and external monitoring of sites.

*Endpoints:* The primary endpoint will be:

1. recrudescent *P. falciparum* within 42 days after correction for re-infections using PCR genotyping of polymorphic parasite loci19, 20 in children with falciparum malaria, or

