2. AP (Pyramax) as artesunate 3 mg/kg and pyronaridine tetraphosphate 9 mg/kg once-daily for three days, and
3. AN (Arco) as artemisinin 20 mg/kg and naphthoquine phosphate 8 mg/kg once-daily for three days (as justified above).

Combinations of full, half- or quarter-tablets will be swallowed whole or crushed lightly before administration. AL-treated subjects will be given tablets or suspension with milk; because there is no such recommendation for AP or AN, pharmacokinetic studies our group will perform during 2009 will determine whether these ACTs should also be given with milk. Only the evening AL doses will be unsupervised, being given at home by parents/guardians. Children vomiting within 30 minutes will be re-treated.

Standardized review including microscopy will be scheduled on Days 1, 2, 3, 7, 14, 28 and 42, with all data, including symptoms, unscheduled clinic visits and non-study treatment, entered on detailed case report forms. Children developing uncomplicated or severe malaria will be given DP at the clinic or intramuscular artemether at the local referral hospital, respectively as per the most recent PNG National Treatment Guidelines.23 All blood films will be re-examined by two skilled microscopists blinded to treatment. Slides discrepant for positivity/negativity, speciation or parasitaemia (>3x difference) will be adjudicated by a senior microscopist. The primary endpoints constitute ACPR under WHO-recommended assessment.24 Early treatment failure (ETF) will be taken as the development of severity or an inadequate parasitological response by Day 3. Any child developing parasitaemia between Days 4 and 42 will be considered late parasitological failure (LPF) or, if febrile, late clinical failure (LCF).

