At baseline and each subsequent visit, a finger-prick blood smear and filter paper blood spot will be taken, in addition to a 250 μL mixed capillary EDTA sample which will be centrifuged and the plasma separated. In addition, a 3-5 mL blood sample will be taken by venepuncture at baseline, day 7 and 28 for antimalarial drug assay. If a child presents with fever or has a positive blood film for malaria at other times, a single blood sample will also be taken – this will normally replace the day 28 sample if there is a re-infection/recrudescence which means the child has reached a pre-specified endpoint. The total volume of blood taken from any child will be <15 mL over 6 weeks. Although there is evidence that Day 7 plasma drug concentrations are independently associated with response for lumefantrine- and PQ-based ACT,25 there has been no study that has looked at pyronaridine or naphthoquine, or simultaneously incorporated other potentially important variables such as baseline *P. falciparum* parasitaemia in predictive models. Our finding that baseline parasitaemia predicted outcome in DP-treated patients8 should also be assessed simultaneously with other parasite- and drug-specific factors in a large patient sample and using other long-half life partner drugs. We did not identify anthropometric features that predicted outcome in our previous trial and postulate the same result with the newer regimens. Plasma drug concentrations at the time of treatment failure have been used qualitatively to identify resistant parasites, but no formal *in vivo* MIC estimate the has been derived.25

We have developed high performance liquid chromatography assays for lumefantrine, naphthoquine and pyronaridine,but now have access to liquid chromatography-mass spectrometry which allows greater assay sensitivity with a smaller sample volume and increased throughput. Day 7 and follow-up samples on the day of reappearance of parasitaemia will be taken from trial patients, centrifuged promptly, and separated plasma kept and transported frozen until assayed at Curtin University. Batches of each treatment will also be retained for assay of content. We have *in vitro* parasite culture facilities at Yagaum and these can be set up at Vunapope. We will utilise the *Plasmodium* lactate dehydrogenase colorimetric assay for drug sensitivity testing.

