*Background:* We have developed HFGMF gametocyte detection based on the unique metabolism of iron in the parasite and commercially available magnetic separation columns (Miltenyi Biotech). The method relies on magnetic concentration of gametocytes which are then identified more readily on a smear (see Figure 2) than by conventional expert microscopy.29 It has a similar sensitivity to reverse transcriptase PCR (RTPCR, data submitted; see Table), but is much quicker and cheaper.

[figure not shown]

| Gametocyte density | HFGMF (time taken) | Thick film (time taken) | RT-PCR |
| --- | --- | --- | --- |
| 2,970/µL | Positive (<1 minute) | Positive (<1 minute) | Positive |
| 297/µL | Positive (<1 minute) | Positive (7 minutes) | Positive |
| 29.7/µL | Positive (<1 minute) | Positive (28 minutes) | Positive |
| 2.97/µL | Positive (9 minutes) | Negative | Positive |
| 0.297/µL | Negative | Negative | Negative  HFGMF detection at 3/μL |

The method could be used to quantify the gametocidal efficacy of ACT assuming that transmission is unlikely at a gametocyte density <3/μL,30 a threshold detectable by HFGMF but not microscopy.

*Methods:* We will take a small additional sample of mixed capillary blood at each follow-up visit from 25 children in each treatment and species arm on which HFGMF and RTPCR will be performed as well as conventional microscopy. The differences in gametocyte carriage by detection method over time between treatment arms will be determined using General Linear Modelling for repeated measures, applying square-root transformation to allow for the effect of zero values on the density distribution at each time point and identifying important non-treatment-related covariates.

**Sub-study 2: Duration of post-treatment prophylaxis using passive case detection of symptomatic malaria during the six months after trial follow-up** *(Secondary Aim 5)*

*Hypothesis:* The duration of post-treatment prophylaxis for AL, AP and AN is a function of the t½*e* of the non-artemisinin partner drug alone.

*Background:* For some long half-life drugs such as piperaquine, urinary excretion studies suggest unexpected persistence of low plasma concentrations.31 In addition, the antimalarial activity of atovaquone in sera is sustained beyond that predicted by its pharmacokinetic properties.32 Whether these sorts of effects are of clinical importance in ACT-treated patients is unknown, even for DP.

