**ETHICAL ISSUES**

*i) Administration of a non-standard treatment for malaria:*  Two-thirds of the children will receive a non-standard treatment for malaria. However, both AP and AN have been well tested and shown to be fully effective in a variety of other countries and AN is already available in PNG. It is important for future antimalarial treatment policy to have up-to-date data from PNG children on alternative therapies if combinations such as AL start to fail.

*ii) Informed consent and child assent:* The parents/guardians of all participants will give informed verbal and written consent. Children who are able to understand and communicate at an appropriate level will be given a basic outline of the study and will not be recruited if there is clear evidence of non-assent to study procedures.

*iii) Painful and unpleasant procedures (finger pricks, venesection):* These may cause a small amount of pain and bruising. The risk of infection is negligible.

*iv) Volume of blood sampling:* The total volume of blood taken over 6 weeks will be <15mL, representing approximately 2% of a child’s haematocrit. This is not a physiologically significant amount and it should be replaced quickly after successful treatment of malaria.

*v) Arrangements for adverse events during the trial:* Trained health care staff will be at each site during working hours and contactable by mobile phone out of hours if necessary, and a physician will be either on site or also available for telephone consultation if a child develops or presents with any adverse event. If the adverse event is considered severe,

1. the child will be transferred promptly to the nearest major hospital for further management
2. the principal investigators will be informed of the nature of the event within 24 hours
3. the local study physicians and principal investigators will determine whether it is not related, possibly related or definitely related to allocated treatment, or unknown
4. the principal investigators will notify each event to the Data and Safety Monitoring Committee who will consider whether the protocol should be modified as a result of such events. The PNG IMR Institutional Review Board will also be notified promptly of such events using the standard format for such occurrences.

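### The venous range of 3 to 5 mL per draw, with the capillary samples, allows 11 to 17 mL per child, and its upper part does not fit the stated limit of under 15 mL

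*Protocol*

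**What the plan says.** All the volumes below are in the Protocol.

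- **Venous blood** (Research Plan, Main Study, Clinical/laboratory procedures): "a 3-5 mL blood sample will be taken by venepuncture at baseline, day 7 and 28 for antimalarial drug assay". This comes on top of the capillary sampling.
- **Capillary blood** (same section): at baseline and every later visit, a smear and a filter-paper spot are taken, "in addition to a 250 μL mixed capillary EDTA sample which will be centrifuged and the plasma separated".
- **Visits** (same section): "Standardized review including microscopy will be scheduled on Days 1, 2, 3, 7, 14, 28 and 42". With Day 0 that makes eight sampling occasions.
- **Limit** (same section): "The total volume of blood taken from any child will be <15 mL over 6 weeks".
- **Limit repeated** (Ethical Issues, item iv): "The total volume of blood taken over 6 weeks will be <15mL, representing approximately 2% of a child", the percentage being expressed against the child's haematocrit.

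Other blood is taken with no volume given: for haemoglobin and glucose at Day 0, for the smears and spots, and for a single unscheduled sample if a child has fever or a positive film at another time. Sub-study 1 (Methods) adds to this for 25 children in each treatment and species arm: "We will take a small additional sample of mixed capillary blood at each follow-up visit".

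**The concern.** The limit is stated for any child, and it is repeated in Ethical Issues to support the statement that the blood loss is not physiologically significant. The trial enrols children from six months of age. A limit given in those terms should hold for every draw volume that the procedures allow. Here the upper part of the permitted venous range does not fit under it, and no sentence tells staff how to choose a volume so that it does. At stake are a possible departure from a commitment in the ethics section and, for some children, a Day 28 visit at which no draw volume satisfies both statements. Sample size, power, alpha and the endpoints are not involved.

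**Working it through.** **Inputs** (all from Clinical/laboratory procedures): three venous draws (baseline, Day 7, Day 28) of 3 to 5 mL each; one capillary sample of 0.25 mL at Day 0 and on Days 1, 2, 3, 7, 14, 28 and 42, so eight samples; limit under 15 mL.

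**The Protocol's figure.** The limit of under 15 mL cannot be reproduced as the maximum of the written schedule. It is met over only part of the range.

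**Step 1, capillary blood.** 8 × 0.25 = 2.0 mL.

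**Step 2, total by draw volume** (3 × draw + 2.0):

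| Each venous draw | Venous sum | Total | Under 15 mL? |
| --- | --- | --- | --- |
| 3 mL | 9 mL | 11 mL | yes |
| 4 mL | 12 mL | 14 mL | yes |
| 5 mL | 15 mL | 17 mL | no, 2 mL over |

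**Step 3, what the limit requires.** The venous sum must be below 15 − 2 = 13 mL, a mean below 13 / 3 = 4.33 mL per draw.

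**Step 4, a permitted sequence that cannot be completed.** With 5 mL at baseline and 5 mL on Day 7, the Day 28 draw must be below 13 − 10 = 3 mL, which is under the written minimum. At exactly 3 mL the total is 5 + 5 + 3 + 2 = 15.0 mL, still not below 15.

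**Step 5, more lenient counting.**
- Venous blood alone: 3 × 5 = 15 mL, already not below 15.
- No capillary sample on the three venepuncture days: five capillary samples, 5 × 0.25 = 1.25 mL, so 10.25 to 16.25 mL.
- An unscheduled sample that replaces Day 28, assumed to be 3 to 5 mL as well: still three venous draws, so 11 to 17 mL.

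The top of the range exceeds or reaches the limit on each count.

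**Step 6, what is left out.** The haemoglobin and glucose blood, smears, spots, Sub-study 1 samples and unscheduled samples have no stated volume. Counting them can only raise the totals. If an unscheduled sample of 3 to 5 mL (an assumption) were taken in addition to Day 28, the total would be 4 × 3 + 2 = 14 mL to 4 × 5 + 2 = 22 mL.

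**Step 7, the percentage.** Taking 15 mL as about 2%, as Ethical Issues does, 17 mL is 17 / 15 × 2% = 2.27%, or about 2.3%.

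**The case against.** A per-draw range under an overall cap is not in itself a contradiction. The limit stands in the same paragraph as the draw volumes and can be read as governing them: staff draw within 3 to 5 mL and keep the sum below 15 mL. Draws of 3 or 4 mL do so. The Protocol also says that its newer mass-spectrometry assay needs less sample, which makes 5 mL draws less likely, and Operational principles states "We will conduct the study using standard operating procedures"; those procedures, which are not shown, may fix a tube volume.

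Much of this stands. A reader might infer that the schedule must break the limit, or that the sponsor added up the volumes wrongly. The document supports neither: a compliant schedule exists within the written range, and the limit is given as a bound, not as a sum. Nor does it support inferring that children would be harmed, since an excess of 2 mL moves the Protocol's own percentage only from about 2% to about 2.3%. The total of 22 mL rests on an assumed volume for an unscheduled sample and should not be quoted as the Protocol's figure.

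The objection does not remove the mismatch. The limit constrains the sum, but nothing says how the draws are to be adjusted, and two early draws at the permitted maximum leave no valid third draw. A tube volume set elsewhere would still leave part of the written range unusable.

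**Conclusion.** The point holds as an unreconciled range and cap. The quantified samples total 11 to 17 mL per child, and the limit of under 15 mL holds only when the three venous draws sum to less than 13 mL. The excess at the top of the range is 2 mL before the samples with no stated volume are counted. The written schedule permits a breach but does not force one.

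The result rests on the stated volumes and on all eight visits and all three venous draws taking place. A child who reaches an endpoint early or misses visits gives less blood. The point is minor, and it is worth correcting because the ethics section relies on the figure.

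**What to change.** In Clinical/laboratory procedures, set the venous draw at 3 mL, the minimum that the Protocol already accepts. The quantified total is then 11 mL, leaving just under 4 mL for the haemoglobin and glucose blood, smears, spots, Sub-study 1 samples and any unscheduled sample. Add that an unscheduled sample counts towards the limit, and that the Day 28 draw is reduced or omitted where needed to stay below it. An extra 3 mL unscheduled draw would bring the quantified total to 14 mL, which is why that rule is needed.

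Narrowing the range to 3 to 4 mL would not be enough: at 4 mL the quantified total is 14 mL, leaving less than 1 mL for everything else.

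The cost is one volume and one sentence, with less plasma per draw and, for some children, a smaller or missing Day 28 sample. The Protocol states no minimum assay volume, so the laboratory should confirm that 3 mL is enough. The planned Cox regression uses Day 7 drug concentrations, so giving up a Day 28 draw would not affect that predictor.

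If the laboratory needs up to 5 mL per draw, restate the ceiling in both places as at least 17 mL plus the samples with no stated volume, and correct the percentage in Ethical Issues, item iv (about 2.3% on its own scale for 17 mL). The cost is a slightly less favourable figure in the ethics section.

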2. appearance of any *P. vivax* parasitaemia within 42 days after treatment for vivax malaria.

Secondary endpoints in falciparum malaria will be:

1. reappearance of PCR-uncorrected *P. falciparum* parasitemia,
2. appearance of any *P. vivax* parasitemia, and
3. appearance of *P. falciparum* gametocytes, all within 42 days.

Secondary endpoints in vivax malaria will be:

1. reappearance of any *P. vivax* parasitemia within 28 days, and
2. appearance of *P. vivax* gametocytes within 42 days.

Other secondary endpoints for each *Plasmodium* species will be initial fever and parasite clearance times (the times to the first of two consecutive assessments at which the child was afebrile and slide-negative, respectively), and drug safety including haemoglobin levels.

*Sample sizes:* Sample size calculations21 for the present trial are based on the assumptions that i) the *P. falciparum* Day 42 PCR-corrected ACPR for AL is 95.2%8 with a non-inferiority margin of 5% for AP and AN, ii) the *P. vivax* Day 42 uncorrected ACPR for AP and AN is at least double the 30.3% found previously for AL (as for DP in the original trial8), iii) there will be equal numbers in each treatment arm, and iv) there will be a 25% attrition rate:

| Study | Type | Total *n* | *n*/group with drop-outs | Power | Α |
| --- | --- | --- | --- | --- | --- |
| *P. falciparum* | Non-inferiority | 515 | 220 | >80% | 0.05 (one-tailed) |
| *P. vivax* | Superiority | 122 | 60 | >90% | 0.05 (two-tailed) |

*Subjects:* Children aged 0.5-5 years with an axillary temperature >37.5°C or fever during the previous 24 hours will be screened using on-site blood film microscopy. Those with either *P. falciparum* (>1000 asexual parasites/μL whole blood) or *P. vivax* (>250/μL) will be eligible if they have i) no features of severity,22 ii) not taken a study drug in the previous 28 days, iii) no clinical (including anthropometric) or laboratory evidence of another infection or co-morbidity including malnutrition. Informed consent will be obtained from parents/guardians.

*Clinical/laboratory procedures:* An initial (Day 0) history will be taken and physical examination performed. Blood will be taken for measurement of haemoglobin and glucose. Treatment allocation will be by computer-generated randomized design in blocks of 24 by site:

1. AL (Novartis Pharma, Basel, Switzerland) as artemether 1.7 mg/kg and lumefantrine 10 mg/kg twice-daily for three days,

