*Interim analysis:* Although the AN regimen to be used in the trial has been developed using detailed efficacy and safety assessment, a validated assay and conventional pharmacokinetic modelling in PNG children, we will perform an interim analysis after the first 50 children have received this form of treatment. This analysis will be done by the Data and Safety Monitoring Committee ([name] (UPNG), [name] (UWA) and [name] UWA – statistician) who will decide whether the AN arm should be retained for the rest of the trial. The criteria to be used will be i) day 3 parasitaemia positive >25% of children, ii) gametocyte carriage >25% on day 7 and/or iii) >25% attrition rate by day 7.

If AN is withdrawn, children in this arm will be switched to DP (dihydroartemisinin 2.5 mg/kg and piperaquine phosphate 20 mg/kg daily for three days; Sigma Tau, Rome, Italy) given with milk at each dose. DP was one of the arms in our original treatment trial8 and is currently recommended second-line treatment in PNG for uncomplicated malaria in children. However, there has been the suggestion that cure rates might improve if fat were co-administered with this form of ACT to enhance bioavailability,28 as it is with AL. As per the Manufacturer’s instructions, DP was administered with water in the original trial.8 All study procedures will remain the same for children in this group.

*Data analysis:* Statistical analysis will be by *a priori* plan. Per-protocol analyses will include children with complete follow-up or a confirmed treatment failure, and will exclude those treated for malaria without confirmatory microscopy or who defaulted from follow-up despite repeated attempts at contact. These excluded patients will be retained in modified intention-to-treat analyses utilizing:

1. a worst-case approach (ETF assumed for Day 3 exclusions, LPF/LCF otherwise) and
2. a best-case approach (all missing blood films assumed parasite-negative).8

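### In the *P. falciparum* non-inferiority comparison, both modified intention-to-treat analyses impute the same outcome in every arm, so neither tests how missing data could change the difference from AL

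*Protocol*

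**What the plan says.** The Data analysis paragraph of the protocol's Research Plan (Main Study) limits the per-protocol set to children who completed follow-up or had a confirmed failure. It leaves out defaulters and children given malaria treatment with no microscopy to confirm it. These children come back in two modified intention-to-treat analyses: "a worst-case approach (ETF assumed for Day 3 exclusions, LPF/LCF otherwise") and "a best-case approach (all missing blood films assumed parasite-negative"). Each rule applies to all arms alike.

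The Sample sizes paragraph fixes the comparison these analyses feed: "Day 42 PCR-corrected ACPR for AL is 95.2%8 with a non-inferiority margin of 5% for AP and AN", with "there will be equal numbers in each treatment arm" and "there will be a 25% attrition rate". The *P. falciparum* row of the table gives 220 children per group including drop-outs and a one-tailed 5% level. The primary endpoint is recrudescence "within 42 days after correction for re-infections using PCR genotyping".

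The protocol does not say which analysis set carries the non-inferiority conclusion, and it does not describe the two imputations as limits on a between-arm difference.

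**The concern.** A sensitivity analysis for missing outcomes in a non-inferiority comparison should ask whether the conclusion survives if the missing children on the new drug did worse than those on AL. Scoring all missing children as failures, or all as successes, gives both arms the same block of identical outcomes. When loss is equal, this pulls the arms together while the margin stays where it was. When loss is unequal, the all-failure version turns the difference in attrition into an apparent difference in efficacy.

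At stake is whether agreement between the per-protocol result and these two analyses can be read as robustness. At 25% attrition a quarter of the outcomes are imputed, so the choice of rule can decide the result.

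**Working it through.** **Inputs.** All from the Sample sizes paragraph: AL ACPR 95.2%; margin 5 points, so a drug at the margin has 90.2%; 220 per arm; 25% attrition; one-sided 5%. As a check on this reading, the total of 515 is recovered to within about 2% as a two-arm total by a Farrington-Manning calculation for 80% power (254 per arm, about 507).

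**Assumptions.** The protocol states no non-inferiority decision rule and gives no attrition by arm. I use a Day 42 risk difference with a one-sided 95% Wald limit, data missing at random, and imputed late failures counted as failures on the PCR-corrected endpoint.

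**Formulae.** For true ACPR p and loss a:
- worst-case ACPR = p(1 − a)
- best-case ACPR = p(1 − a) + a
- with equal loss, both differences = (1 − a) × true difference
- chance of passing = Φ[(0.05 − difference)/SE − 1.645], with SE from the two imputed proportions on 220 per arm (per-protocol: observed proportions on 165 per arm).

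**Drug at the margin, 25% loss in both arms**
- Worst-case: 0.952 × 0.75 = 0.714 v 0.902 × 0.75 = 0.6765; difference 3.75 points; SE 0.0439; Φ(0.285 − 1.645) = 8.7% (simulation 8.9%).
- Best-case: 0.964 v 0.9265; difference 3.75 points; SE 0.0216; Φ(0.578 − 1.645) = 14.3% (simulation 16.1%).
- Per-protocol: difference 5.0 points; 5.0% (simulation 5.7%).

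Against the undiluted difference, the 5-point margin acts as 5/0.75 = 6.7 points. Simulations used 400,000 trials per scenario.

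**Other attrition patterns, drug still at the margin (normal approximation)**

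| Loss, AL v new | Worst-case difference | Worst-case passes | Best-case passes |
| --- | --- | --- | --- |
| 10% v 10% | 4.5 | 6.6% | 7.6% |
| 25% v 25% | 3.75 | 8.7% | 14.3% |
| 27.5% v 22.5% | −0.9 | 38.0% | 10.8% |
| 30% v 20% | −5.5 | 77.5% | 8.0% |
| 24% v 26% | 5.6 | 3.7% | 15.9% |
| 23% v 27% | 7.5 | 1.4% | 17.7% |
| 20% v 30% | 13.0 | 0.02% | 23.6% |

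Simulation for the 10% row gives 6.8% and 8.8%.

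**When each analysis stops diluting.** Worst-case widens the gap only if 0.902 × new-drug loss exceeds 0.952 × AL loss, a ratio of about 1.06; around a mean of 25% that is about 1.4 points more loss on the new drug. Best-case widens it only if 0.048 × AL loss exceeds 0.098 × new-drug loss, so AL loss must be about twice the new drug's. Both cannot hold at once, so at least one of the two always dilutes the deficit.

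**What neither analysis covers.** With 25% missing in each arm and an observed 5-point deficit, imputing in opposite directions gives 0.964 − 0.6765 = +28.75 points at one end and 0.714 − 0.9265 = −21.25 points at the other. Both planned analyses give +3.75.

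**Equally effective drug, 25% loss in both arms.** The chance of passing is 68% per-protocol, 31% worst-case and 88% best-case. The two imputations can therefore disagree when efficacy is identical.

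**The case against.** **Do both analyses always make non-inferiority too easy?** A reader might infer this, but it is not so. The worst-case analysis is conservative once loss on the new drug exceeds AL's by more than about 1.4 points. The protocol's only arm-specific attrition criterion concerns AN (the interim analysis), which is that direction. It is also the harsher test for an equally effective drug, 31% against 68% per-protocol. Both attrition directions must therefore be shown.

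**Is the trial's false-positive rate 9% to 16%?** The document does not support that. Those rates apply only if an imputed analysis is used to declare non-inferiority, and no set is named as decisive. Requiring the per-protocol analysis as well would hold the error near 5% if data are missing at random. What remains is that missing at random is the very assumption a sensitivity analysis should test. It is doubtful for children treated for malaria without microscopy, whose missing films the best-case rule then scores as negative.

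**Does the pair claim to bracket the difference?** The protocol makes no such claim. All-failure and all-success imputation do bound each arm's own ACPR, which is useful because the Background judges drugs against a WHO requirement of more than 95%.

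**Is this a matter for the statistical analysis plan?** Further sensitivity analyses may be there, and their absence here is no finding. The point concerns two rules that the protocol itself fixes.

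The named methods are Kaplan-Meier and log-rank, so the exact percentages depend on my assumed rule. The shrinkage to 3.75 points does not depend on the choice of confidence limit.

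**Conclusion.** The point holds for the *P. falciparum* non-inferiority comparison. Same-outcome imputation in every arm does not test how missing data could alter the difference from AL. At the planned common 25% attrition it dilutes a 5-point deficit to 3.75 points in both analyses, and a drug at the margin would pass about 9% (worst-case) or 14-16% (best-case) of the time; at 10% attrition, about 7% and 8-9%. With unequal loss the worst-case result follows attrition more than efficacy, in either direction.

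The practical consequence is conditional: it arises if either analysis is offered as support for non-inferiority. In the *P. vivax* superiority comparison, dilution under equal attrition is conservative, so the point does not carry over.

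**What to change.** 1. State that neither same-direction analysis alone supports non-inferiority. Keep the pair as descriptive limits on each arm's own ACPR.
2. As the sensitivity check on the per-protocol non-inferiority result, add an arm-specific tipping-point analysis in all randomised children. Start from each arm's own observed failure rate (missing at random), raise the failure probability among missing AP or AN children until non-inferiority is lost, and report that point.
3. Do not start from the AL rate in every arm. For a drug at the margin that gives 0.75 × 90.2 + 0.25 × 95.2 = 91.45 against 95.2, the same 3.75-point shrinkage. Each arm's own rate leaves the difference at 5.0.
4. The opposed extreme (missing AP/AN fail, missing AL succeed) may be shown for reference only. At 25% loss an equally effective drug would show 96.4% v 71.4% and have practically no chance of passing.

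The cost is a few sentences and a little programming, with no new data. The downside is a sensitivity result that will look less favourable than the present pair.
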